# Bridging hospital to home for children with medical complexity and their families: an observational prospective cohort study protocol to assess the effectiveness of an innovative transitional care unit in the Netherlands (BRIDGE study)

**DOI:** 10.1136/bmjopen-2024-093693

**Published:** 2025-04-19

**Keywords:** Hospitals, Hospital to Home Transition, Organisation of health services

## Abstract

**Introduction:**

Children with Medical Complexities (CMC) often require 24/7 expert care, which frequently necessitates prolonged (re)admissions to a university medical centre (UMC), thereby impeding discharge to home. The transition from hospital to home for CMC is a multifaceted process with numerous challenges and obstacles. This protocol describes the evaluation of an innovative transitional care unit (TCU), where families can stay together in a home-like environment between hospital and home. Under the supervision of healthcare professionals, parents are supported in preparing for a sustainable home situation. We hypothesise that an intermediate stay at the Jeroen Pit Huis (JPH) will have a favourable effect on healthcare consumption, patient, parent and family-relevant outcomes in comparison to discharge directly from a hospital ward to home. Therefore, the purpose of this study is to compare the transition via the TCU JPH versus transition from hospital ward to home as provided elsewhere for CMC patients in the Netherlands.

**Methods and analysis:**

This observational prospective cohort study compares patients who transition directly from hospital to home with those who transition via the TCU. The control group comprises five UMCs in the Netherlands. Data will be collected by extracting information from electronic health records and through online questionnaires. Parents complete questionnaires at three time points: on discharge home, 3 months and 12 months postdischarge. Bayesian inverse probability weighting will be used to control for confounding effects and analyse the results.

**Ethics and dissemination:**

Ethical approval was granted by the Amsterdam UMC Medical Ethics Committee (W20_220#20.007). The need for ethical approval was waived by all other participating UMCs. Results will be disseminated through peer-reviewed scientific journals and conference presentations. The insights gained from this study will contribute to the development of a national care pathway to enhance transitional care for CMC and their families in the future.

**Trial registration number:**

NCT06599398 (ClinicalTrials.gov) - Bridging Hospital to Home for CMC and Their Families.

STRENGTHS AND LIMITATIONS OF THIS STUDYA prospective cohort design allows for the systematic comparison of children with medical complexity who are transferred home via the transitional care unit vs directly from hospital to home.Longitudinal follow-up over 12 months enables assessment of sustained intervention effects.The use of Bayesian Inverse Probability Weighting (BIPW) strengthens causal inference by adjusting for confounding.A limitation is that despite the use of BIPW, there may still be unmeasured confounding variables that could affect the results.High questionnaire burden may lead to selective participation, especially among highly stressed parents.

## Introduction

 Children with Medical Complexity (CMC) are characterised by one or more complex chronic conditions, technology dependency, high family needs and significant healthcare resource utilisation.^1^ The transition from hospital to home (H2H) for CMC is a multifaceted process with numerous challenges. The child’s primary caregivers, hereafter referred to as parents, transition from receiving care in the hospital to becoming the primary and most responsible caregivers at home. A study by van de Riet *et al*. revealed that parents experience and express needs across several domains—some of which remain unmet—including learning complex nursing care, gaining confidence, coordinating care, improving communication and access to information.^2^ Furthermore, families require support in accessing resources, finding support systems, navigating emotional challenges such as fatigue, fear, isolation and guilt, building effective relationships with professionals and adjusting their perspectives by establishing new routines.^2 3^

Due to these extensive needs, parents report feeling unsupported and unprepared during the transition to home.^4^,^7^ To address these challenges, various postdischarge interventions have been developed, including nurse visits and coaching,^8 9^ telephone follow-up calls^10^ and telemedicine.^11 12^ Other strategies for improving the H2H transition include the implementation of comprehensive care plans, complex care programmes and integrated delivery models.^13^ Comprehensive care plans facilitate better communication between parents and healthcare professionals,^14^,^16^ while complex care programmes reduce hospital-specific patient costs and also enhance parental satisfaction and family-centred care.^17^,^19^ In the Netherlands, an innovative transitional care unit (TCU), called the Jeroen Pit Huis (JPH), is developed to improve H2H care and address family needs.^20^

This TCU is situated on the premises of the Amsterdam University Medical Center (UMC) and intends to mimic the home situation. Families can stay together while practising in, and adapting to, their new reality until they are ready to transition home. The length of TCU stay varies from a minimum of 1 week to a maximum of 3 months. A multidisciplinary team of healthcare experts (nurses, psychosocial care workers, family counsellors and paediatricians) gradually guides parents towards taking on the role of their child’s primary caregiver. In this TCU, a structured care pathway is employed, addressing a critical gap in current healthcare systems that professionals recognise as essential.^21^,^23^ To date, the effectiveness of this novel care facility remains unknown.

The purpose of this study is to compare the transition via the TCU JPH versus transition from hospital ward to home as provided elsewhere for CMC patients in the Netherlands. We hypothesise that the continuous presence of parents in a home-like setting and the structured care pathway within the JPH will have a favourable effect on healthcare consumption, patient, parent and family-relevant outcomes, compared with discharge directly from a hospital ward to home.

## Methods and analysis

### Design

An observational prospective cohort study design was chosen, because it is not feasible to randomly assign patients to the intervention, as children are placed in a ward or the JPH based on the UMC where they are admitted. Random assignment to specific hospitals is not feasible given the practical impossibilities and negative impact of relocating children and families out of their own usual living environment.

The Strengthening the Reporting of Observational Studies in Epidemiology guideline will be used to report the study.^24^

### Setting

This study will be conducted in five Dutch UMCs and the TCU JPH, all part of the TCU consortium. The TCU consortium is a collaborative initiative between five UMCs, parents, patient associations and home care organisations.

The UMCs include the Amsterdam UMC – Emma Children’s Hospital, Erasmus MC (EMC) – Sophia Children’s Hospital, Radboudumc Nijmegen (Rumc) – Amalia Children’s Hospital, UMC Groningen (UMCG) – Beatrix Children’s Hospital and the UMC Utrecht (UMCU) – Wilhelmina Children’s Hospital.

### Intervention group

The JPH is a separate building on the premises of the Amsterdam UMC. This TCU consists of eight separate family apartments and was opened in May 2022. Each apartment has its own bedroom for the child with medical complexity, a master bedroom for parents or caregivers, a living room, a bathroom, a kitchenette, a mezzanine level with a bed and desk for (if necessary) siblings and a private outdoor area. Furthermore, the JPH has different communal areas: a kitchen, living room with various workspaces, relaxation and play, a snuggle room, an adapted bathroom for persons with disabilities, a physiotherapy gym and a garden with playground. The JPH primarily serves children from the Amsterdam UMC, although children can be referred from hospitals in or outside the Amsterdam region.

In the JPH, at least one parent must be present 24/7, and siblings are also welcome to stay in the apartment. The TCU team consists of nurses, family counsellors and paediatricians. Additionally, we collaborate with other healthcare professionals, including allied health professionals, home care providers and pharmacy personnel in both the hospital and home settings. Nursing care and supervision of a dedicated paediatrician is available 24/7. In this form (24/7 parental stay and nursing care under the supervision of paediatricians), the JPH is unique in the Netherlands. During the stay, more and more responsibilities and tasks are gradually transferred to the parents until they become the primary caregivers. This process is guided by a newly developed structured care pathway, which is informed by the parental needs identified within our consortium.^3^ This care pathway outlines the transition process for parents and children as they move from being care recipients to taking on the role of care providers and coordinating their own care. It is organised into seven phases, each with a step-by-step transition plan (see online supplemental file 1 for more details). Personalised treatment goals are established based on the specific needs of both the child and the parents, facilitating a successful transition back home. These needs will vary for each family but can be categorised under overarching domains of care, namely physical, financial, psychological, social, spiritual and practical aspects such as medical devices, legal considerations and future/developmental aspects.

### Control group

The control groups comprise patients and families who undergo the H2H transition directly from the hospital. This includes patients from the other four UMCs of the consortium. Patients from the Amsterdam UMC who transition directly from H2H without an intermediate stay in the JPH will also be included in the control group. Since there is no standardised care path, the H2H transitions vary across the different UMCs and even within different departments. There are no other TCUs in the Netherlands like the JPH; however, Erasmus MC offers one single-room apartment where parents can stay with their child for a weekend before being discharged home.^25^

A visual overview of differences between the intervention group and control group is presented in online supplemental file 1.

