#### Exclusion criteria

Patient requiring end-of-life care.Existence of predominantly social/family issues without serious medical problems in the index patient.Patient with behavioural/psychiatric problems necessitating other types of care.Patient requiring inpatient rehabilitation medical care.Patients discharged via other out-of-hospital facilities other than the JPH.

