Health system (secondary) outcomes	Healthcare consumption	Length of hospital/JPH stay, number of (PICU) readmissions, emergency department visits and visits to the general practitioner (GP) or GP emergency services	12 months of follow-up

JPH, Jeroen Pit Huis ; PICU, pediatrics intensive care unit; PTSD, post-traumatic stress disorder.

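### Arms are set by the route a child completes, so any delay before JPH entry biases the length-of-stay comparison, in a direction that depends on when the clock starts

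*Protocol article*

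**What the plan says.** The protocol article describes the arms in several places.

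- **Abstract, Methods and analysis:** the study "compares patients who transition directly from hospital to home with those who transition via the TCU".
- **Control group:** "The control groups comprise patients and families who undergo the H2H transition directly from the hospital". Amsterdam UMC patients "who transition directly from H2H without an intermediate stay in the JPH will also be included in the control group".
- **Design:** randomisation is called infeasible because "children are placed in a ward or the JPH based on the UMC where they are admitted".
- **Intervention group:** the JPH mainly serves Amsterdam UMC, "although children can be referred from hospitals in or outside the Amsterdam region". It has eight apartments.
- **Exclusion criteria:** one criterion also depends on the eventual route: "Patients discharged via other out-of-hospital facilities other than the JPH".

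A child becomes eligible while still in hospital and not yet able to go home (Inclusion criteria). Parents may be recruited on the ward or during the JPH stay (Recruitment).

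Table 1 lists "Length of hospital/JPH stay, number of (PICU) readmissions" among the healthcare consumption outcomes, which are secondary. The caption of Figure 2 also names hospital length of stay. The primary outcome is parental distress at discharge home.

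Under Bayesian inverse probability weighting, treatment is a single yes/no variable. It is predicted from confounders, and the weighted outcome model contains treatment alone.

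**The concern.** Arm membership is known only after the fact. Take two similar Amsterdam children who become eligible on the same day. If one goes home before any transfer to the JPH, that child is a control with a short stay. If the other is still in hospital when transfer happens, that child is a JPH case, and the days before transfer could only be accrued by not going home. This is the usual structure of immortal-time bias. It needs no formal waiting list, only a non-zero interval between eligibility and JPH entry.

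Length of stay is directly exposed, because the outcome (time to going home) helps to decide the arm. Propensity weights built on baseline confounders balance what is known at the start. They cannot undo a classification that depends on what happens later.

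The Design section gives the admitting hospital as the basis of placement. If that were the arm definition, the problem would not arise. The Control group and Intervention group sections show that it is not: some Amsterdam children are controls, and children from elsewhere can enter the JPH.

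**Working it through.** **No plan figure to reproduce.** The article gives no length of stay, waiting time or number of Amsterdam controls. The only figure used from it is the planned 50 JPH and 100 control children (Sample size). All times below are assumptions, and the JPH is given no true effect.

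**Set-up.** T is the time from eligibility to going home and W is the time from eligibility to a JPH place. An Amsterdam child is a JPH case if W < T and otherwise a control. Children from other UMCs, with the same distribution of T, bring the controls to 100.

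**Closed form with exponential times.** Let a be the mean of T, b the mean of W, and m = ab/(a + b).

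- Share of Amsterdam children entering the JPH: a/(a + b)
- Mean stay of Amsterdam controls: m
- Mean stay of JPH children: m + a
- Amsterdam controls per 50 JPH children: 50b/a

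With a = 30 and b = 10 days:

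- m = 300/40 = 7.5 days, and the JPH share is 30/40 = 0.75.
- The JPH mean is 7.5 + 30 = 37.5 days.
- Amsterdam controls number 50 × 10/30 = 16.7, leaving 83.3 from other UMCs.
- The pooled control mean is (16.7 × 7.5 + 83.3 × 30)/100 = 26.25 days.
- The false difference is 37.5 − 26.25 = 11.25 days, which equals 1.5m.

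The same formula gives 6.4 days for a mean wait of 5 days and 18.0 days for a mean wait of 20 days.

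**Wider range by simulation.** T was given a constant discharge hazard (exponential) or one rising with time (gamma, shape 2), with mean 30 or 60 days. W was exponential with mean 3, 7, 14 or 21 days. Selected results, in days, JPH minus pooled controls:

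| Hazard | Mean T | Mean W | Total days from eligibility | JPH days counted from JPH entry |
|---|---|---|---|---|
| constant | 30 | 3 | +4.1 | +1.4 |
| constant | 30 | 14 | +14.3 | +4.8 |
| constant | 60 | 21 | +23.3 | +7.8 |
| rising | 60 | 3 | +0.7 | −2.2 |
| rising | 30 | 14 | +7.1 | −2.5 |
| rising | 60 | 21 | +10.8 | −5.1 |

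Over all 16 settings, the false difference in total days runs from +0.7 to +23.3. The standard error of a 50 versus 100 comparison is 3.7 to 10.4 days. With the clock started at JPH entry, the difference is +1.4 to +7.8 under a constant hazard and −1.8 to −5.1 under a rising one, so the sign can change.

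**Does the weighting help?** One baseline confounder was added. Mean T was 45 days at its average value, the mean wait was 14 days, and the ratio was 1:2. Weights followed the article's formula. The false difference fell only from +18.6 to +15.9 days. Within Amsterdam alone, +48.8 days remained after weighting.

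**Do the alternatives work?** With the arm fixed at eligibility (Amsterdam against other UMCs), the difference was −0.08 to +0.07 days in every setting. With JPH entry as a time-dependent exposure, the crude discharge rate ratio was 1.00 under a constant hazard. It was 1.7 to 6.2 under a rising one, so that model must also condition on time since eligibility.

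**The case against.** The strongest reply is that no delay before JPH transfer is documented, and the article's own figures do not show scarcity. Eight apartments over 1.5 years (about 548 days) give 8 × 548 = 4,384 apartment-days. Fifty stays of an assumed 30 days use 1,500, or about 34%. Only stays near the three-month maximum (50 × 90 = 4,500) would fill the unit. Amsterdam children may also bypass the JPH for other reasons, such as the rule that a parent be present around the clock. That would be confounding, which the plan addresses by weighting and whose residue Study limitations admits. This stands as far as size goes: families outside the study also use the apartments, but the documents do not show how long children wait. It does not remove the mechanism, which needs only some interval.

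A reader might infer that the JPH must look worse on length of stay. The documents do not support that, because the start of the clock is not given and recruitment during the JPH stay is allowed.

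A reader might add the minimum stay to the bias: "The length of TCU stay varies from a minimum of 1 week to a maximum of 3 months". That minimum is part of the intervention, so any extra days it causes are a real effect.

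A reader might also conclude that a child who enters the JPH, returns to the ward and goes home from there belongs to neither arm. The Control group wording keeps that child out of the Amsterdam controls, and the stated hypothesis contrasts an intermediate JPH stay with direct discharge, so the JPH arm is the natural reading. At most this is an ambiguity. Figure 1, the supplements and the full protocol, none of them shown, may settle it along with the clock.

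**Conclusion.** The point holds in a limited form. The article states affirmatively that the arm follows the completed route, and it describes an analysis with one fixed treatment indicator and baseline weights. Applied to length of stay, that gives a biased comparison wherever there is an interval between eligibility and JPH entry, and the weighting leaves most of the bias in place. The Design section's account of placement also conflicts with the Control group and Intervention group sections.

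Counted in total hospital plus JPH days from admission or eligibility, the bias runs against the JPH. Counted from JPH entry, or from inclusion during the JPH stay, it can run either way. The size is unknown: +0.7 to +23.3 days in total stay under the assumed times, and small if transfer is quick. These figures assume that every Amsterdam child is a candidate for the JPH and that T and W are independent. They illustrate the mechanism and are not estimates for this study.

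It would be wrong to extend the immortal-time argument to every outcome. Distress at discharge home and the 3- and 12-month measures are timed from discharge in both arms. For these, classification by route is a selection problem.

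**What to change.** 1. Set one time zero in all five UMCs: the date a child first meets the inclusion criteria on the ward, including for children recruited later in the JPH. Count length of stay as total hospital plus JPH days from that date.
2. Keep the comparison by actual route, and state that any child who enters the JPH stays in the JPH arm, including after an early exit or a return to the ward.
3. For length of stay, add one analysis free of this bias. Either fix the arm at time zero (Amsterdam UMC against the other UMCs), or treat JPH entry as a time-dependent exposure in a model that conditions on time since eligibility. Classifying by planned route would help only in part, because a plan is made after eligibility and the other UMCs have no equivalent.
4. Reconcile the Design, Intervention group and Control group sections on what determines the arm.

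The cost is two dates per child (eligibility and JPH entry), partly retrospective because recruitment began in December 2023, plus a few sentences and one added analysis. The contrast by admitting UMC is diluted by Amsterdam children who never enter the JPH and by any referred in from another UMC. It also still carries differences between hospitals, so it supplements the main comparison and does not replace it.

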### Participants

Potentially eligible participants are children admitted to one of the five UMCs. We will apply the following inclusion and exclusion criteria; a flowchart to further depict this is shown in figure 1.

**Figure 1 F1:**
[figure not shown]
Flow chart of the inclusion process.

#### Inclusion criteria

Age: at term (older than 37 weeks corrected gestational age) and younger than 18 years.Admitted to the hospital with (a deterioration of) a chronic complex condition (CCC) and/or (expected) continuous dependence on technology after discharge (see online supplemental file 2 for detailed overview of CCC diagnosis).Expected need for specialised medical and/or allied healthcare after discharge.Discharge home not yet possible due to organisation circumstances, care-related or family circumstances (for more specifics see online supplemental file 3).A stable medical condition and/or a set treatment regimen, defined as one or more of the following situations:A patent, safe airway to remain in the home situation, whether or not by means of a trachea cannula.Adequate respiration, whether or not by means of (intermittent) support with oxygen, non-invasive ventilation or invasive ventilation via a trachea cannula.Neurologically stable condition that may include temporary neurological impairments (such as seizures) not interfering (potentially life-threatening) with other vital functions such as respiration or circulation.Drug treatment that can be given at home where (if applicable): a nasogastric, duodenal or jejunal tube and/or a percutaneous endoscopic gastrostomy (PEG) tube or gastrostomy is in situ, or if necessary, a 'home-proof' intravenous access is guaranteed.In case of enteral tube feeding, the nasogastric, duodenal or jejunal tube and/or a PEG tube or gastrostomy is in situ, and the feeding schedule may be built up, reduced or variable if there are no contraindications for this. In case of parenteral nutrition, this must be organised according to the home situation.

#### Exclusion criteria

Patient requiring end-of-life care.Existence of predominantly social/family issues without serious medical problems in the index patient.Patient with behavioural/psychiatric problems necessitating other types of care.Patient requiring inpatient rehabilitation medical care.Patients discharged via other out-of-hospital facilities other than the JPH.

### Patient and public involvement

To ensure the inclusion of parents’ perspectives in the design of this study, close collaboration was maintained in the consortium with a parent caring for a CMC. She actively served as a representative of a patient advocacy organisation for children with complex medical needs (BS). She is engaged in research meetings and contributed to the development of the protocol. Furthermore, she took part in the pilot testing of the (self-constructed) questionnaires, provided feedback and, together with HH, made improvements to ensure feasibility. She provided insights and input for the parent and caregiver information flyer, letter and video clip.

